### Ethics and dissemination

Ethics approval was obtained from the *Comité d’éthique de la recherche sectoriel en réadaptation et intégration sociale, CIUSSS de la Capitale Nationale* (#2019–1731 – CER CIUSSS-CN) in March 2019. Any modification to the protocol will be submitted to the ethic committee for approval and to clinicaltrials.org. Written informed consent will be obtained from all of the participants, after they read the information brochure describing the project and the potential risks and benefits and after discussing with the investigator if they have any questions. Every participant will be informed that he/she is free to leave the project at any moment. All numeric data collected will be safely stored in files protected with a password, and hard copies will be kept in locked file cabinets. Only study investigators will have access to the data at the completion of the trial. Results of the RCT will be published in a peer-reviewed journal and de-identified data will be available on a public repository at the time of publication. Results will also be communicated through scientific meetings. The International Committee of Medical Journal Editors criteria for authorship will be followed and no professional writer will be involved.

### Harms

Participants will be asked to write down any minor side effects or adverse events that occurred through the 1-week intervention in the logbook. They will also have a phone number and an e-mail address to reach the PT if they experience any major adverse events or if they have any questions during the week. The PT will then be able to direct the participant to the appropriate resource or give appropriate advices.

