**ASSE****SS****ME****NTS:**							
**Baseline demographic information**		**●**					
**Physical functioning** (ODI)		**●**		**●**	**●**	**●**	**●**
**Pain** (NRS)		**●**		**●**	**●**	**●**	**●**
**Pain-related fear** (TSK-11)		**●**		**●**	**●**	**●**	**●**
**Self-efficacy** (CDSES −6)		**●**		**●**	**●**	**●**	**●**
**Perception of change** (GRoC)				**●**	**●**	**●**	**●**
**Number of steps walked per day**			**●** (daily)				

A_0_: first contact with participants; A_1_: baseline assessment; I: 7-day intervention; A_2_: assessment 1 week after baseline; A_3_: assessment 4 weeks after baseline; A_4_: assessment 12 weeks after baseline; A_5_: assessment 24 weeks after baseline; ODI: ODI-French Canadian Version; NRS: pain numerical rating scale; TSK: 11-item version of Tampa Scale of Kinesiophobia; CDSES − 6: Chronic Disease Self-Efficacy Scale - Short-Version and GRoC: global rating of change

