#### Timeline

First visit: baseline measurements and intervention

*Baseline:* At the baseline assessment, demographic characteristics will be collected before participants complete self-administered questionnaires on symptoms and functional limitations (ODI-French Canadian Version) [15, 17], pain-related fear (11-item version of Tampa Scale of Kinesiophobia – TSK-11) [18] and self-efficacy measured with the Chronic Disease Self-Efficacy Scale - Short-Version (CDSES-6) [19]. Pain intensity will be measured using an 11-point numerical rating scale (NRS) [20, 21] (average previous week [1-week]). These 4 questionnaires will serve as outcome measures (see “Outcome measures” section). The STarT Back Screening Tool [22] and the Canadian minimal dataset for low back pain [23] will be completed to characterise the participants recruited. After baseline assessment*,* participants will be assigned randomly to one of three intervention programs.

*Intervention:* To start, participants will meet a physical therapist (PT) to receive their assigned program (60-min meeting). For participants assigned to the thermal therapy groups (thermal therapy alone and thermal therapy + exercises), a heatwrap (ThermaCare®, Pfizer inc., New York, USA) will be applied onto the lower lumbar spine area, whereas in participants assigned to the control group, a sham non-heat lumbar belt will be applied. In addition, the physical therapist will teach an exercise program to the participants assigned to the “thermal care + exercises” group.
2Intervention program

After the 1st visit, participants will take part in their assigned 7-day intervention program. Every day, participants will indicate in a logbook their average pain level during the day and the adherence to their program. A fitness watch will be given to each participant to record the number of steps walked per day during intervention week. They will be asked to avoid meeting a health care professional for their ALBP during the 7 day-intervention program. After the 7 days, they will be free to do so.
3Second visit – short-term follow-up

A 2nd visit will be realized approximatively 7 days after the 1st visit, and ODI, TSK-11, CDSES-6, average 1-week pain intensity and a global rating of change (GRoC) [24] will be measured to determine the short-term effect of thermal therapy.
4Long-term follow-ups

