At 4, 12 and 24 weeks after baseline assessment, the average 1-week pain intensity, TSK-11, ODI, CDSES-6 and GRoC will be completed electronically by each participant. Participants will also report the use of other interventions after the completion of the 7-day intervention (e.g. medication, psychological support, health care professional, exercises training).

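### Adverse events are recorded only in an open logbook during the 7-day intervention; the week 4, 12 and 24 forms list no adverse-event item, so late or persisting events have no dedicated field

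*Protocol article*

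**What the plan says.** The Harms section names one recording instrument and one period: "Participants will be asked to write down any minor side effects or adverse events that occurred through the 1-week intervention in the logbook". It adds a phone number and e-mail address for the physical therapist (PT), to be used "if they experience any major adverse events or if they have any questions during the week". What follows such a contact is described in one sentence: "The PT will then be able to direct the participant to the appropriate resource or give appropriate advices".

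The Timeline section describes the same logbook without mentioning harms: "Every day, participants will indicate in a logbook their average pain level during the day and the adherence to their program".

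Follow-up goes well past the intervention week. The last assessment in the Table 1 legend is "A_5_: assessment 24 weeks after baseline". For the three later time points the Timeline section lists the content: "At 4, 12 and 24 weeks after baseline assessment, the average 1-week pain intensity, TSK-11, ODI, CDSES-6 and GRoC will be completed electronically". It then adds: "Participants will also report the use of other interventions after the completion of the 7-day intervention". Exercise training is one of its examples of such interventions. Table 1 has no row for harms at any time point.

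**The concern.** The article does not merely leave harm collection open. It fixes a period, the intervention week, and separately lists what the later forms contain. If both are followed as written, three kinds of event have no place to be recorded as adverse events:

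- a skin reaction that shows itself after the last heatwrap application;
- a problem that began in the week and has not resolved;
- a flare in a participant who carries on with the exercises after day 7.

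What is at stake is the trial's ability to describe delayed or persisting events by arm. The trial presents its contribution as the long-term effect of heat with or without exercises, so readers of the results will probably ask about tolerability over the same period. The primary analysis of disability is not affected.

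The logbook is also open rather than solicited, and under Randomization / blinding the risks of heat are explained only to participants in the thermal groups. Those participants may be readier than controls to write down a skin complaint. A question put in the same words to every arm would reduce that difference, though it would not remove it.

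**Working it through.** The article states no figure on this point, so the check sets its sections side by side.

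| Time point | Outcome data listed | Adverse-event collection listed |
|---|---|---|
| Intervention week | Daily pain, adherence, steps | Logbook (Harms section only); contact with the PT for major events |
| Visit 2, about day 7 | ODI, TSK-11, CDSES-6, pain, GRoC | None |
| Weeks 4, 12 and 24 | The same five measures, plus other interventions used | None |

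**Step 1: the window.** The Harms section ties the logbook to the 1-week intervention. The invitation to contact the PT also refers to that week. No other section extends either one.

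**Step 2: the later forms.** Three electronic forms are planned. None has an adverse-event item in the Timeline section or in Table 1. The time between the end of the intervention and the last assessment is 24 − 1 = 23 weeks.

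**Step 3: exposure after day 7.** The assigned programs end at 7 days. The exercise group has by then been taught a home program, and the Timeline section expects that some participants may use exercise training afterwards, since it asks about it. Some exposure may therefore continue after recording stops. How much cannot be known from the article.

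**Step 4: what the existing items would show.** ODI, the pain scale, and GRoC, which runs down to −7, would register worsening. The question on other interventions would register new care. None of these is described as asking what happened, when it began, or whether it might relate to treatment. They leave a trace of a late problem but do not identify it as an adverse event.

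**Step 5: consistency within week 1.** The Harms section puts adverse events in the logbook, the Timeline section describes that logbook as holding pain and adherence, and Table 1 omits harms. These are not contradictory, because the Timeline list need not be complete, but the three places should be aligned.

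**The case against.** The strongest reply is that the recording window matches the exposure. Heat, sham belt and exercises are assigned for 7 days, so every day of assigned treatment falls inside the recorded period. The objectives name disability, pain, fear, self-efficacy, perceived change and steps. No long-term safety objective or benefit-harm comparison is declared, so the 7-day window contradicts nothing in the plan. This stands, and it keeps the point at the level of an improvement.

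A reader might go further and infer that the trial cannot report serious harms. The text does not support that. In the Harms sentence the word minor may qualify side effects only, so a major event in the week could also be written in the logbook. The contact route to the PT is additional to the logbook. Nothing says that such contacts go unrecorded, and a condensed article may leave that step to the full protocol.

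A reader might also measure the gap by the share of follow-up weeks covered, or by the upper confidence limit on risk when no events are seen. Neither measures it. The first counts calendar time although all assigned exposure is covered. The second assumes complete recording, so it describes what a trial of this size could show after the fix.

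Finally, a question about skin problems or exercise flares at visit 2 could reveal the allocation to the blinded evaluator. That is a fair objection to a careless version of the remedy, and the fix below allows for it.

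**Conclusion.** The point holds in a limited form. The article confines stated adverse-event recording to an open logbook in the intervention week, and none of the three later forms lists an adverse-event item. Events that begin or persist after the last application have no dedicated field during the remaining 23 weeks, and late worsening is seen only indirectly through outcome scores and reported use of care.

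No number of missed events can be given, because the article offers no event rates. The conclusion assumes that the Harms section, the Timeline section and Table 1 give the collection schedule as it will be run. If the full protocol already has an adverse-event item on the later forms, the remaining task is to align the article with it. The finding does not show that serious harms will go unreported or that a stated objective is contradicted. It is a worthwhile, nearly free improvement.

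**What to change.** In the Timeline and Harms sections, with a matching row in Table 1:

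1. Add one short solicited item, in the same words for all three arms, to the electronic forms at weeks 4, 12 and 24. It should ask about any new or worse problem since the last form, its date, and whether medical care was needed.
2. Use the same item at visit 2, self-completed and routed so that the blinded evaluator does not see the answer.
3. State that events reported to the PT by phone or e-mail are entered in the trial data.
4. State in the Timeline section that the logbook also records adverse events, so that it agrees with the Harms section.
5. Report events by arm, separating the intervention week from later follow-up.

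The cost is one brief item on questionnaires already being sent and a record of PT contacts. There are two downsides. Many late events will be unrelated to treatment, so relatedness must be noted. The visit 2 item could also unblind the evaluator if it is not handled separately. These changes concern data capture only and alter no rule on treatment or clinical care.

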## Discussion

This will be the first RCT to evaluate the long-term effect of thermal therapy, combined or not with exercises, in the treatment of ALBP. To date, it is known that thermal therapy [9] contributes to reduce pain in ALBP in the short-term [5] and its use is recommended in the latest Clinical Guideline for LBP management [5]. However, the effect of these interventions in the long term remains unknown. This lack of knowledge is problematic, because thermal therapy may only produce a transient analgesia, having no influence on the long term trajectory of LBP. Importantly however, thermal therapy might potentiate other interventions that could be more effective on the long-term, such as exercises. A better understanding of the time-dependent effect of thermal therapy and exercises in ALBP will allow improving the management of LBP, and thus help reduce the huge socioeconomic burden of this condition [1, 2].

## Data Availability

De-identified data will be made available on a public repository at the time of publication.

## Abbreviations

ALBP/ CLBP: Acute/chronic low back pain
CDSES-6: Chronic Disease Self-Efficacy Scale - Short-Version
GRoC: Global rating of change
ICC: Intraclass correlation coefficient
MCID: Minimal clinically important difference
NRS: Numerical rating scale
ODI: Oswestry Disability Index
PT: Physical therapist
RCT: Randomized controlled trial
RMDQ: Roland-Morris Disability Questionnaire
TSK-11: 11-item version of Tampa Scale of Kinesiophobia
